#### Sleep Quality Measurement

Sleep quality will be measured using the Epworth Sleepiness Scale (ESS), which evaluates 8 items, each from 0 to 3 points, where 0 indicates the patient would never nod off, 1 indicates a small probability of nodding off or falling asleep, 2 indicates a moderate probability of nodding off or falling asleep, and 3 indicates a high probability of falling asleep. A score from 1 to 6 on the scale is considered regular sleep, one from 7 to 8 points is considered mild sleepiness, and one from 9 to 24 points at a pathological (abnormal) drowsiness [19].

#### Quality of Life Measurement

Quality of life will be measured using a Quebec Sleep Questionnaire (QSQ), which has been validated for the Hispanic population. It contains 32 items focused on measuring daily sleepiness (7,16,20,27), daytime symptoms (1,10,11,14,17,18,19,26,29), nighttime symptoms (4,9,21,25,28,30), emotions (5,6,8,15,24), and social interactions (2,3,12,13). The questionnaire will be applied basally and after 12-month follow-up [20].

#### Physical Activity Measurement

To measure physical activity, the International Physical Activity Questionnaire will be applied. The questionnaire contains 7 items that asses at the physical activity carried out in the past 7 days (hours, minutes, and days of the week). Physical activity will be classified after considering the metabolic equivalent of task values according to the activity (measurement unit of the test). Physical activity is classified in 3 categories: low, moderate, and high (25). It will be measured at the beginning of the trial, and after 6 and 12 months [21].

### Nutritional Intervention Description

#### Group With MD Adjusted Using Mexican Food

The patients in the MD group will be given a normocaloric, personalized diet with the following distribution, 15%-20% protein, 50%-55% carbohydrates, 25%-30% fats, and <7% saturated fats, according to the recommendations for patients with OSA. The Mifflin-St Jeor equation will be applied to calculate the caloric requirements. At the beginning of the intervention, 24-hour reminders will be established to know dietary habits and adjust the diet to the patients’ preferences, customs, and budget. A dietary plan will be designed using equivalent foods. The equivalents will be chosen from the Mexican system of equivalent foods, considering portions, amounts, and preparation of each food. In it, typical foods of the Mexican diet can be found, along with their most common preparation and presentation; for instance: grilled, fried, baked, and uncooked (raw), among others [22].

The MD includes a variety of typical foods from European countries. Therefore, it is necessary to analyze their nutritional characteristics before adapting the diet to Mexican citizens, particularly those patients with OSA taking part in this study. After reviewing the literature, foods belonging to the Mexican diet were identified to show similar characteristics as those in the MD. As part of the adaptation, a comparative chart showing European and Mexican foods was created using the major food groups. Table 1 shows the most representative foods and their adaptation to the Mexican diet, which is explained simply to the patients.

**Table 1 table1:** Mediterranean-Mexican food: proposal for the adaptation of the Mediterranean diet with Mexican food.

Food group/equivalent	Mediterranean diet	Foods in Mexico	Suggested portions and frequency of consumption
Fruit and vegetables	Fruit: grapes, watermelon, strawberries, oranges Vegetables: artichokes, asparagus, lettuce, bell peppers, spinach, broccoli	Fruit: guava, orange, mango, mamey, papaya, blackberry, banana Vegetables: nopal, chayote, cucumber, mushrooms, purslane, quelites, chard, watercress, zucchini, bell pepper, green beans, jicama	Fruit: 1-2 servings per main meal Vegetables: >2 servings per main meal Total: at least 5 servings per day
Healthy Fats	Olive oil, olives, hazelnuts, almonds	Avocado, nuts, peanuts, corn oil, sunflower oil, pumpkin seeds, pistachios, sesame seeds	Olive oil: in every main meal Nuts, seeds, olives, avocado: 1-2 servings per day
Cereals	Whole wheat bread, pasta, rice, couscous	Whole wheat bread, pasta, rice, corn tortilla, oats, amaranth	Bread, pasta, rice, tortilla, oats: 1-2 servings per main meal
Tubers	Potatoes, sweet potatoes	Potatoes, sweet potatoes, yuca	Potatoes, sweet potatoes, yuca: <3 servings per week
Legumes	Lentils, chickpeas, beans, peas	Lentils, beans, chickpeas	Lentils, beans, chickpeas: >2 servings per week
Animal-based foods	Fish and seafood: salmon, cod, squid, mussels, shrimp, oysters Low-fat dairy: yogurt, cheese, milk White meat: chicken, hen, turkey Eggs Red and processed meats: beef, pork, cold cuts	Fish and seafood: tuna, sardines, trout, red snapper, tilapia Low-fat dairy: yogurt, cheese, milk, cottage cheese, curd White meat: chicken, hen, turkey Red and processed meats: beef, pork, cold cuts	Fish: >2 servings per week Low-fat dairy: 2 servings per day White meat: 2 servings per week Eggs: 2-4 servings per week Red meat: <2 servings per week Processed meats: <1 serving per week

This table provides examples of foods characteristic of the general Mexican population. It may vary according to the region of Mexico, seasonality, and accessibility for each patient.

In addition to the equivalency chart including the food groups of both diets, a healthy eating plate MD (see Figure 1), was created as the strategy has been effective in Mexico, where the main foods for a healthy diet are presented in a plate [23]. From this strategy, a plate of MD in Mexico was designed, adapting foods that must be consumed according to the region, culture, preferences, and budget, considering easy access for patients with OSA.

**Figure 1 figure1:**
[figure not shown]
Mediterranean diet plate adapted with Mexican food.

To reinforce the meal plan given to this group, preestablished menus were designed containing foods typical in the MD, such as fruit, vegetables, whole grains, cereals, and white meat. The menus also promoted the intake of vegetable oils and common dried fruit in Mexico. The menus were designed to reach 1200, 1400, 1600, 1800, 2002, and 2200 calories. This group will also continue their common treatment with their physician or group of health care professionals as usual.

#### Assessment of Adherence to the MD With Mexican Food

Adherence to MD will be measured using the 14-point Mediterranean diet adherence screener (MEDAS) questionnaire, consisting of 12 questions on the consumption frequency of foods and 2 questions on intake habits of foods considered part of the MD [24]. In this instrument, each question is scored 0 or 1. One point is given for using olive oil as the main source of fat for cooking, preferring white meat over red meat, or for consuming (1) 4 or more spoons of olive oil per day, (2) 2 or more vegetable portions per day, (3) 3 or more pieces of fruit per day, (4) less than 1 portion of red meat or sausage per day, (5) less than 1 portion of animal fat per day, (6) less than 1 sugary drink per day, (7) 7 or fewer glasses of red wine per week, (8) 3 or more portions of legumes per week, (9) 3 or more portions of fish per week, (10) fewer than 2 cakes or commercial baked goods per week, (11) 3 or more portions of nuts per week, and (12) a plate of traditional tomato, garlic and onion sauce twice or more a week. The total score ranges between 0 and 14 and allows to identify 3 levels of MD, low (0-6), medium (7-8), and high (≥9).

#### SD Group

Patients in the control group will be given a normocaloric diet with the following energy distribution: 15%-20% protein, 50%-55% carbohydrates, 25%-30% fats, and <7% saturated fats, per the guidelines for adult patients with OSA. The Mifflin-St Jeor equation will be applied to identify the caloric requirements of each patient. The energy needs and distribution will be administered as individual nutritional guidance regarding sleep hygiene measures and type of diet for weight loss according to age, sex, current body weight, and present comorbidities. At the beginning of the intervention, 24-hour reminders will be set to know the daily diet. Patients will be given a pamphlet to reinforce healthy eating, and they will continue nutritional consultations with their physicians. This group will also continue the traditional treatment with their physician or group of health care professionals as usual.

#### Follow-Up and Study Procedures

At the beginning of the trial and after 12 months, laboratory data (glucose and lipid profiles), clinical data, arterial blood pressure records, anthropometry, body composition, and dietary records of the previous 3 days will be obtained, along with the quality of life and sleep survey. All the patients will receive the written results and explanation in each clinical consultation, as shown in Figure 2.

**Figure 2 figure2:**
[figure not shown]
Follow-Up and Study Procedures.

Follow-up will continue after 3, 6, and 12 months for MD and 6 and 12 months for SD diet participants, who will attend a consultation with a nutritionist and medical team. In order to measure the adherence to the diet in both groups, the patients will register the 3 days before their clinical visit, 2 registrations from Monday to Friday, and one on weekends. At each visit, nutritional guidelines will be given to improve adherence to the nutritional intervention. The study follow-up is shown in Table 2.

**Table 2 table2:** Study follow-up and procedure in patients with obstructive sleep apnea in both groups.

Time collection	Baseline	3 months	6 months	12 months
Collection of sociodemographic data	MD^a^ and SD^b^	—^c^	—	—
Medical history	MD and SD	—	—	—
Medical evaluation	MD and SD	—	MD and SD	MD and SD
Biochemical data	MD and SD	—	—	MD and SD
Arterial blood pressure and Anthropometric and body composition measurements	MD and SD	MD	MD and SD	MD and SD
Sleepiness with Epworth sleepiness scale	MD and SD	MD and SD	MD and SD	MD and SD
Quality of life with Quebec Sleep Questionnaire (QSQ)	MD and SD	—	—	MD and SD
Physical activity with IPAQ^d^ Questionnaire	MD and SD	—	MD and SD	MD and SD
Adherence to the diet intervention with records of the previous 3 days	MD and SD	MD	MD and SD	MD and SD
Adherence to the diet intervention with MEDAS^e^ Questionnaire	MD and SD	MD	MD and SD	MD and SD
Phone call follow-up	—	SD	—	—

^a^MD: Mediterranean diet.

^b^SD: standard diet.

^c^Not applicable.

^d^IPAQ: International Physical Activity Questionnaire.

^e^MEDAS: 14-point Mediterranean diet adherence screener questionnaire.

### Primary Outcomes

The primary objective of this clinical trial is to evaluate the effect of the MD adapted to the Mexican diet versus an SD treatment on metabolic risk indicators in patients with OSA (body weight, fasting glucose, lipid profile, WC, and body composition).

The secondary outcomes are to evaluate the effect of the intervention on:

Sleep quality through ESS.Changes in quality of life through QSQ.Adherence to nutritional therapy intervention through records of meals corresponding to previous and MEDAS questionnaires.

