## Methods

### Study and Population Assignment

A randomized, 2-arm clinical trial will be conducted with patients with OSA from the Regional Hospital, Mexican Social Security Institute (Instituto Mexicano del Seguro Social [IMSS]) in Mexico City with a 12-month follow-up.

The sample size was calculated using the formula for difference in proportions, considering a CI of 95% and a power of 80%. Weight loss is expected in 58% of the sample corresponding to the group given an MD adapted to the Mexican population and in 30% of the group consuming a standard diet, as previously reported in the literature. A sample size of 49 patients per group was obtained and, considering losses of 20%, the total number of patients will be 120 [16].

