#### Biochemical Indicator Measurement

Venous blood samples will be taken after fasting for 8-10 hours to measure glucose, lipid profile (cholesterol, triglycerides, high-density-lipoprotein cholesterol, and low-density-lipoprotein cholesterol). Measurements will be recorded during the first consultations and after 6 and 12 months.

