#### Anthropometric and Body Composition Measurements

Body composition will be measured by bioimpedance, using an InBody 120 composition analyzer, to obtain fat percentage, fat mass, lean mass, and total body water. Body weight and height will be measured with the same analyzer. The patient must wear as little clothing as possible, without any metal objects (bracelets, earrings, rings, belts, and others). The patient will face forward, place their feet on the metal plates, and extend their arms forward to hold the metal bars at a 90º angle. Height will be measured using an InBody ultrasound stadiometer while the patient is in an upright anatomical position. Anthropometry will be recorded by 2 nutritionists previously standardized, using the method proposed by Habitch and according to the specifications previously [17,18]. The BMI will be obtained from height and weight.

Waist circumference will be measured using a measuring tape halfway between the lowest rib and the top of the right hipbone. The average value of the second and third measurements will be used for analysis. Measurements will be taken during the first consultation and after 3, 6, and 12 months.

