### Statistical Analysis

The statistical analysis of the data will be carried out using SPSS (version 27; IBM Corp). The study population will be described using the background, clinical, and pathological variables to characterize the sample of participants with OSA. The Kolmogorov–Smirnov test will be used to identify the distribution of quantitative variables. For variables with normal distribution measures of central tendency and dispersion will be estimated. For variables with a free distribution mean and IQR will be used. Measures of frequency and percentages will be used for sociodemographic and clinical qualitative variables, as well as those of patient proportion with and without glycemic control, and with and without cognitive impairment. A chi-square test will be used to compare the effect of MD versus SD on parameters of control and uncontrol of metabolic risk indicators. Depending on the data distribution, a Student *t* test will be used to compare quantitative variables with parametric distribution between groups, and a Mann-Whitney *U* test will be conducted for free-distribution variables. A multivariate logistic regression analysis will be performed, including the achievement of metabolic indicator control goals, sleep quality, and quality of life as outcome variables. This analysis will be adjusted for other variables that may be statistically significant in the bivariate analysis, such as sex, age, and comorbidities, among others. Statistically significant differences between groups will be considered when the value of *P*<.05.

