## Discussion

### Anticipated Findings

This protocol aims to measure the impact of an MD adapted to the Mexican population on cardiovascular risk indicators, such as glucose, lipid profile, body weight, and blood pressure in patients with OSA. In addition, as secondary objectives we seek to evaluate the effect of the MD on sleep quality and quality of life, as well as the improvement in diet quality.

There is enough evidence on the cardioprotective effect of MD, which is not only proven in European countries: there are clinical trials evaluating MD adapted to the Chilean population suffering metabolic syndrome [25]. It has been proven that interventions aimed at lifestyle improve AHI, showing a reduction by –4.55 events per hour and improving weight and BMI among patients with OSA; however, no effect on sleep and life quality has been found [26]. Despite the ample evidence supporting the cardioprotective benefits of the MD, its evaluation has been predominantly focused on patients with obesity, diabetes, and, to a lesser extent, patients with OSA. The impact of adapting the MD diet with food in Mexico has been examined to a lesser extent.

The relationship between cardiometabolic risk factors and sleep duration has been previously reported in 47 patients with OSA in a rural community in the southeastern United States. The authors reported that shorter sleep duration was associated with an increased risk of hypertension, obesity, and impaired metabolic indicators. [27]. The results of this study suggest that an MD intervention with a preference for fruit, vegetables, high-fiber cereals, and white meat protein may improve cardiometabolic indicators.

Obesity and related diseases, like diabetes, hypertension, and dyslipidemia, represent a greater risk for patients with OSA. Then, CPAP treatment combined with weight loss is an effective strategy to reduce cardiovascular risk [28]. Adaptation to the patient's tastes, customs, and budget is necessary to improve adherence to MD. This study seeks to adequate MD to the Mexican diet to make it accessible, since typical MD includes foods considered high-priced for the population receiving care at public health care institutions in Mexico.

Furthermore, improvement in cardiometabolic indicators, such as glucose, lipid profile, and weight loss, is likely. Patients are expected to lose 5%-10% of their initial body weight, as reported by similar interventions [12].

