Sleep quality in patients with OSA could improve after the proposed nutritional intervention, while the number of obstructive respiratory events could be reduced given that the size of the oropharyngeal lumen is reduced because of body fat loss [29]. Besides the reduction in obesity, the diet is expected to improve fasting glucose, arterial blood pressure, and dyslipidemia in patients with OSA taking part in the trial. We also expect this trial to positively affect daytime drowsiness in the patients and improve their quality of life. This clinical trial would be one of the few conducted in Mexico with patients with OSA where the implementation of low-cost strategies aims at improving cardiometabolic indicators and quality of life of those patients with OSA who receive care at public health care institutions in Mexico.

Among the limitations of the present study, adherence to the MD could be found; therefore, it is relevant to adapt the diet to the economic resources, habits, and customs, which allows an adequate adherence to the MD. A personalized diet and a timely follow-up will be provided to reinforce adherence to the nutritional intervention. It has also been shown that the use of CPAP is limited in the population with OSA, since they do not consider it necessary for their condition or it is difficult to use it to sleep adequately [30]. One of the potential limitations of the study is the use of a self-reported tool to collect sleep quality information. There will be limitations to the generalizability of the effect of the intervention, as it will be a single-center study. In this sense, as one of the main variables is to measure the improvement in sleep quality, this could be improved with the use of CPAP, so its use will be recorded in the follow-up visits, to include it in the multivariate analysis.

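### About eleven metabolic variables are jointly primary at an unadjusted P<.05, and the sample size rests on a weight-loss proportion that the protocol never defines as an outcome

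*Protocol article*

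**What the plan says.** Under Primary Outcomes, the protocol article states the objective as the effect of the adapted MD against the standard diet on "metabolic risk indicators in patients with OSA (body weight, fasting glucose, lipid profile, WC, and body composition"). Two of these headings cover several measurements. Biochemical Indicator Measurement specifies "lipid profile (cholesterol, triglycerides, high-density-lipoprotein cholesterol, and low-density-lipoprotein cholesterol"), and Anthropometric and Body Composition Measurements uses bioimpedance "to obtain fat percentage, fat mass, lean mass, and total body water".

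Statistical Analysis plans a chi-square test of controlled against uncontrolled indicators, a t test or Mann-Whitney test of quantitative values, and logistic regression on reaching control goals. One rule covers them all: "Statistically significant differences between groups will be considered when the value of" P is below .05. No variable, form of analysis or visit is singled out as primary.

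Study and Population Assignment sizes the trial on a difference in proportions with 80% power. It says "Weight loss is expected in 58% of the sample corresponding to the group given an MD adapted to the Mexican population", against 30% on the standard diet, and concludes: "A sample size of 49 patients per group was obtained and, considering losses of 20%, the total number of patients will be 120". It does not say how much loss counts or by when.

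In the Discussion, Anticipated Findings restates the aim as "cardiovascular risk indicators, such as glucose, lipid profile, body weight, and blood pressure in patients with OSA". Blood pressure is not in the Primary Outcomes list.

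**The concern.** If success on the primary objective may be claimed from any of 11 variables, each at P<.05, the trial's error rate is not 5%. The authors could also choose, after seeing the data, which variable, which form (value or controlled/uncontrolled) and which visit to present as the main result.

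The power statement has a related gap. It is for a yes/no version of body weight that is not listed as an outcome and cannot be computed from the text, because no threshold or time point is given. A reader of the final report could not tell which analysis had 80% power. The other ten variables have no power statement at all.

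**Working it through.** **1. Number of primary variables.** Body weight 1 + fasting glucose 1 + lipids 4 + waist circumference 1 + body composition 4 = 11.

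**2. The plan's own sample size.** Inputs from Study and Population Assignment: 58% and 30%, 95% confidence, 80% power. I take the test as two-sided, because the article does not say. The mean proportion is (0.58 + 0.30)/2 = 0.44. The pooled formula is

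n = [1.960 × √(2 × 0.44 × 0.56) + 0.842 × √(0.58 × 0.42 + 0.30 × 0.70)]² / (0.58 − 0.30)²

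= [1.960 × 0.7020 + 0.842 × 0.6735]² / 0.0784 ≈ 3.774 / 0.0784 ≈ 48.1, so 49 per group.

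This matches the stated figure. Power at 49 per group is 80.7%. The arithmetic is sound.

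**3. Chance of at least one P<.05 among 11 tests at one visit, with no true effect.**

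- Independent tests: 1 − 0.95^11 = 43.1%.
- Correlated tests: the documents give no correlations, so a range of common correlations is assumed and 11 two-sided z tests are simulated (400,000 draws each).

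| Assumed common correlation | At least one P<.05 | At least one favouring MD |
|---|---|---|
| 0 | 43% | 24% (1 − 0.975^11) |
| 0.3 | 37% | 19% |
| 0.5 | 30% | 15% |
| 0.7 | 22% | 11% |
| 0.8 | 18% | 9% |
| 0.9 | 13% | 7% |

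An assumed block pattern (0.7 among the six body measures, 0.4 among the four lipids, 0.2 elsewhere) gives 33%, with 17% favouring MD.

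**4. Cost of keeping all 11 as primary.** With Bonferroni, alpha is 0.05/11 = 0.00455 per test. For the plan's own 58% against 30%, power at 49 per group falls from 80.7% to 48.1%. Restoring 80% needs 84 per group, or 84/0.8 = 105 per group (210 in all) after 20% losses. With one named primary, alpha stays at .05 and the stated size stands.

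**5. Time point.** The follow-up is 12 months, but no section calls 12 months the primary analysis time. The abstract and Biochemical Indicator Measurement put blood tests at 6 and 12 months as well as baseline. Follow-Up and Study Procedures and Table 2 show them at baseline and 12 months only. The possible number of comparisons is therefore unsettled.

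**The case against.** The best defence starts from the sample size. Body weight stands first in the primary list, the trial was sized on a dichotomy of it, and the planned chi-square test of controlled against uncontrolled indicators could carry that dichotomy. On this view the article has an implicit primary and lacks only a cut-off. A multiplicity rule may also sit in an analysis plan that is not shown. Both points have force. A reader might infer that the trial was sized on a different endpoint which the plan never analyses, and the text does not support that. The missing adjustment rule alone would be no finding. But which variable is primary, in what form and when, and how it ties to the sample size, are protocol matters. The article has a section for each and leaves the link open.

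A reader might also infer that a chance positive trial is likely. It is not shown to be. Every single-visit figure is below one half, and 43% is the extreme of independence. Several of these measures come from one analyser and must be correlated. The figure would pass one half only if two visits were both tested and correlations were low (22 independent tests: 1 − 0.95^22 = 68%), and no section says that between-group tests will be run at several visits.

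Two further readings should be set aside:

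- The limitations text calls sleep quality a main variable ("as one of the main variables is to measure the improvement in sleep quality"). This is loose prose. Primary Outcomes makes sleep quality secondary, and the opening of Anticipated Findings repeats that.
- 60 per group less 20% leaves 48, one short of 49. Power at 48 is 79.9% against 80.7%, which is of no consequence. A simple uplift, 49 × 1.2 = 58.8, rounds to 60.

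**Conclusion.** The concern holds, and it should be fixed before analysis. Eleven variables are jointly primary at P<.05 with no ranking, summary measure or primary time point. The single-visit chance of at least one false positive is materially inflated, at about 18% to 43% for assumed common correlations from 0.8 down to 0, with about half of these errors favouring MD. The range rests on assumed correlations, two-sided tests and one test per variable.

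The sample size is correctly calculated, but for a weight-loss proportion that has no threshold or time point and is not named as an outcome. The 80% power is therefore tied to no defined analysis. Blood pressure, present in the Discussion's aim and absent from the primary list, is a smaller inconsistency to correct at the same time.

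**What to change.** Make these changes before any outcome comparison:

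- **Primary.** In Primary Outcomes, name one: the proportion of patients with weight loss at 12 months. Use the threshold behind the 58% and 30% assumption, and compare groups by the planned chi-square test. The stated 49 per group and 80% power then apply to it. The threshold must come from the source used for sizing. The 5% to 10% loss expected in the Discussion is not tied to those percentages. If the source used another time point, justify the assumption for 12 months.
- **Alternative.** If percent weight change is preferred as primary, it needs its own power statement, because the trial was sized on a proportion and the article gives no standard deviation for weight change.
- **Secondary.** Move glucose, lipids, waist, body composition and continuous weight change to secondary at 12 months. Either adjust them by Holm's method or report estimates with 95% confidence intervals and no confirmatory claim.
- **Consistency.** List blood pressure the same way in Primary Outcomes and Anticipated Findings.

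The cost is revised wording in the protocol and a matching registration entry, with no new data or visits. The downside is that fewer results can be called significant. Recruitment has begun and analysis is planned for February 2026, so the change carries weight only if it is made and dated before outcomes are compared.
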